#### Tertiary outcome measures

The tertiary outcome measure will assess reading speed using the WRRT. The WRRT will be measured before prescribing PTLs, with each pair of PTLs, and at the end of the clinical trial in phase 5, as described above. To reduce variability and assess reliability, the test will be administered twice in each condition (with or without tints). The testing order will be ABBA, with A randomly allocated to one of the conditions.

Previous studies have shown that for participants with VS, PTLs and IOs increase reading speed [25, 37] measured on the WRRT. Conventional reading tests [38] are designed for educational use to assess long-term improvement and are commonly used to estimate reading age. These educational tests often use large print that is visually unchallenging and are not suitable for assessing the immediate short-term effect of optometric interventions.

In contrast, the WRRT was designed not for educational use but to assess the immediate effect of optometric interventions [25, 37] and comprises four passages, each taking 1 min to administer. This approach is highly relevant in measuring the effect of PTLs. Research reveals that the WRRT is a valid measurement of within-subject treatment effects and, therefore, well-suited to the research [25].

The specific measurement variable will be scored on a quantitative scale representing the number of words read correctly in 1 min on the WRRT with pair A vs pair B. The analysis will be carried out at the end of the 3-month trial, as participants will complete the WRRT throughout the trial, administered at baseline (referring to the situation before interventions) and at the end of each wearing period (referring to the situation with each intervention). The method of aggregation will be to compare the number of words read and will reveal whether pair A or pair B created the greatest reduction in VS symptoms.

### Participant timeline

See Table 2.

**Table 2 Tab2:**
[figure not shown]
Participant timeline using the SPRIT template

### Sample size

A sample size ($$n$$ = 120) was determined based on the sample size calculation for AB/BA crossover trials described by Jones and Kenward [39]:$$n=\frac{2{({Z}_{1-\beta }+{Z}_{1-\alpha /2})}^{2} {\sigma }_{\omega }^{2}}{{\mu }_{d}^{2}}$$where:$$n$$ = total needed sample size$$({Z}_{1-\beta }+{Z}_{1-\alpha /2})$$ = sum of $$z$$-scores at which the tails of the normal distribution correspond to probabilities $$\alpha$$ and $$\beta$$, where $$\alpha$$ is the desired significance level for hypothesis testing, and $$1-\beta$$ is the desired power of the test$$\sigma$$ = within-subjects standard deviation of symptom scores$${\mu }_{d}$$ = mean difference in scores between control and experimental conditions $$({\mu }_{ctrl}- {\mu }_{expt})$$

This total sample size estimate was calculated using an effect size of half a standard deviation (0.5 SD), 90% power, a 0.05 probability of a type I error ($$n$$ = 88), and an allowance for individuals who might withdraw from the study.

To establish whether an experimental treatment is superior to the control, the convention is to set the significance level (*α*) at 0.05, as recommended by Julious [40]. Furthermore, a statistical power of 0.90 (*β*= 0.10) was selected, as this is the recommended standard for crossover trials [39, 40].

When discussing the effect size for this RCT, it was apparent that there are no prior data to aid the selection of effect size, and this RCT is proposing a new outcome measure. Therefore, it was necessary to investigate existing statistical rationales to assist with this decision. An effect size (standardised mean difference) of 0.5 SD was chosen based on Lakens [41] and Norman et al. [41, 42].

### Recruitment

It is anticipated that most participants will be recruited from the Anglia Ruskin University (ARU) eye clinic by informing self-referred VS participants of this RCT. This clinic has offered specialist services to people with suspected VS for over 10 years and has a reputation for excellence in this field [35]. This will be the initial approach, but as recommended by Loudon et al., if this does not produce the required number, additional steps will be taken [43]. Specifically, publicity will be generated by advertisements placed within the ARU, the ARU eye clinic (including the orthoptist department), and local optical practices with the permission of practice managers and/or owners.

Cash payments will not be made, but PTLs will be provided free of charge for participants of the RCT. A basic spectacle frame will be offered free of charge, with participants able to use a more expensive frame if they fund this themselves. The provision of reduced price/free precision tinted spectacles means that some participants may be included who would not otherwise have been able to afford precision tinted spectacles. Data collection and any optometric testing will only begin after informed consent has been given.

## Assignment of interventions: allocation

### Sequence generation

The sequence generation will use block randomisation, with blocks of 4, from www.sealedenvelope.com. The use of blocks of 4 means that as long as the number of participants is a multiple of 4, there will be an equal number of participants wearing each intervention in the first period (balanced design).

Participants will be told that 50% of participants will receive the optimal colour first and 50% will receive a slightly different colour first. Each participant will swap to the other colour after 1 month of wear.

When the specification of both tints has been determined at the colorimetry assessment, the participant will choose a spectacle frame in which either the optimal or sub-optimal tint will be glazed. A technician (not the research optometrist) will check the frames, lens optical properties, and tint. Each participant will be provided with one spectacle frame which will be reglazed to the other tint at crossover.

The researcher, participants, parents, teachers, etc., will be masked as to whether each participant receives the optimal or sub-optimal tint first. This is possible because during colorimetry, when each colour is selected, colours are changed slowly so that the person being tested adapts to the colour and therefore is unlikely to be aware of the difference in colour appearance of the optimal and sub-optimal tint. Further, participants will receive the first pair of spectacles some weeks after colorimetry, so they will be likely to have forgotten their detailed perceptions during colorimetry.

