**Methods:**

A total of 120 participants aged 9–18 years meeting diagnostic criteria for VS will be recruited from the Anglia Ruskin University Eye Clinic. A widely used instrument, the Intuitive Colorimeter, will be used to select, for each participant, the chromaticity of precision tinted lenses (PTL) that they claim optimally alleviates their symptoms and a similar control colour will also be determined. Participants will be randomised into group 1, receiving spectacles with intervention A (optimal tint) followed by B (sub-optimal tint), or group 2, receiving the two interventions in the order BA. The first intervention will be used for 1 month, followed by a 1-month washout period, the second intervention for 1 month, and then a head-to-head comparison in the clinic with participants invited to keep their preferred pair of spectacles. The primary outcome measurement is symptoms (measured by symptom diaries and symptom questionnaires); the secondary outcome measure is observed school performance (measured by academic behaviour surveys); and the tertiary outcome measure will be reading speed (measured by the WRRT).

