## Design and methods

This will be a single-centre, double-masked randomised controlled crossover trial. There will be a 50:50 allocation ratio to evaluate the superiority of a hypothetically optimal intervention over a sub-optimal intervention.

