### Implementation

Participants will be given participant numbers in sequence. The lead researcher (ZR) will undertake colorimetry and will send the results for each participant to AW. For each participant, AW will provide NT with the PTL specification for the optimal and sub-optimal tints. BE will provide a list of randomisation codes to NT, specifying for each participant number whether the first pair should be the optimal or sub-optimal colour. NT will organise the ordering of the PTL with the dispensing team at Cerium. ZR will conduct all participants’ testing and will be unaware of whether the optimal tint is worn first or second.

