Initially, all data will be checked by scatter plots of raw data. All data will be tested for normality using the Shapiro-Wilk test, and non-parametric data will be transformed to parametric where possible. Simple comparisons will use paired *t*-tests, or the Wilcoxon signed-rank test as appropriate. For more complex analyses, a Mixed-Effects Model for Repeated Measures (MMRM) will be carried out to account for the crossover design, including fixed effects (intervention type, period, and sequence) and random effects (participant variability).

A confirmatory check will be performed to test for order effects (e.g. whether participants who have the optimal tint after the sub-optimal tint have a statistically different outcome from those who have the sub-optimal tint after the optimal tint). If such an effect is found, key analyses will be repeated whilst controlling for the order effect. In addition, an analysis of the effects of the first tint alone will be compared across participants. The analysis will have low power and will be confirmatory, but it is independent of order effects.

Participants for whom there is a complete set of symptom diary data for at least 2 weeks of wear with both interventions will be analysed on an intention-to-treat basis (ITT) [44]. In the unlikely event that any participants are misallocated, then key analyses will also be run according to a per protocol approach. For the symptom questionnaire conducted before enrolment in the trial and for the academic behaviour surveys, data will only be analysed for participants for whom data are available for *both*interventions [44].

Sensitivity analysis will also be carried out to confirm the robustness of the data produced.

The secondary outcome survey measures will be converted to numeric values. Scores will be aggregated and averaged across surveys and then prepared for statistical analysis using the approaches described above. Tertiary outcome measures will be assessed separately as an exploratory analysis. Tertiary outcome measures will undergo reliability testing using the intraclass correlation coefficient, and analysis for order effects using repeated measures ANOVA, before comparing interventions using standard *t*-tests.

All statistical analyses will be conducted using R (version 4.3.1, R Core Team 2023).

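### A fixed, published block size of 4 makes tint order partly predictable to the one masked tester if that tester recognises some tints; undisclosed varying block sizes would close this leak at little cost

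*Protocol article*

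**What the plan says.** Under Sequence generation the article states: "The sequence generation will use block randomisation, with blocks of 4, from www.sealedenvelope.com". Its one stated reason is that a multiple of 4 participants then gives equal numbers on each tint in the first period.

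Design and methods adds: "This will be a single-centre, double-masked randomised controlled crossover trial", and "There will be a 50:50 allocation ratio". No stratification factor is mentioned. The Abstract sets the size: "A total of 120 participants aged" 9 to 18 years.

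Implementation says: "Participants will be given participant numbers in sequence". The randomisation codes are tied to those numbers and pass from one team member to another, who orders the lenses. The lead researcher "will undertake colorimetry and will send the results for each participant to" a colleague, conducts the testing of every participant, and is to remain unaware of which tint comes first. Who will be blinded repeats that this researcher is masked.

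The reasons given for expecting masking to hold (slow colour change with adaptation, and a gap of some weeks before the first spectacles arrive) are framed around what the participant perceives and remembers. They do not address the researcher who ran the colorimetry.

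The Statistical methods section plans a check on the first period: "In addition, an analysis of the effects of the first tint alone will be compared across participants". It calls this check low in power and confirmatory.

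**The concern.** Sequential numbers on a single list let anyone who knows the block size read off block membership: 1–4, 5–8, and so on. Each set holds two participants who start on the optimal tint and two who start on the sub-optimal tint. The block size is in the protocol, so the lead researcher can be taken to know it, and nothing says it is withheld. Keeping the list with other people stops it being read. It does not stop deduction from the block constraint.

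In a two-period crossover, knowing the order means knowing the tint in both periods. A deduced order would therefore unmask the tester for both sides of that participant's comparison. The places where this could matter are the scoring of the Wilkins Rate of Reading Test (WRRT), contact with participants at visits, and the researcher's part in choosing the preferred pair.

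**Working it through.** **The article's own figure.** 120/4 = 30 complete blocks with two of each order, so 60/60 in the first period. The balance statement is correct.

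**Inputs.** Block size 4 (Sequence generation); 1:1 allocation and one centre (Design and methods); numbers in sequence and one tester (Implementation). Two things are assumed: one unstratified list, since no strata are mentioned, and a recognition rate r that is independent between participants and always correct. The article gives no value for r, so a range is shown.

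**What a recognised order tells about its block.** There are 6 equally likely arrangements.
- One order known: the other three members comprise one of the same order and two of the opposite. Each has probability 2/3 of the opposite order, against 1/2 before.
- Two known: they match with probability 1/3, and the other two are then fixed. They differ with probability 2/3, and each remaining member is back at 1/2.
- Three known: the fourth is always fixed.

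**Certain deductions.** For an unrecognised participant, the other three members are all recognised with probability r³ (always decisive). Exactly two are recognised with probability 3r²(1−r), decisive one time in three. The total is r³ + r²(1−r) = r².

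| r (assumed) | Recognised directly, 120r | Unrecognised but certain, r² | Added by deduction, 120(1−r)r² | Total known, r + (1−r)r² |
|---|---|---|---|---|
| 0 | 0 | 0% | 0 | 0% |
| 0.1 | 12 | 1% | 1.08 | 10.9% |
| 0.2 | 24 | 4% | 3.84 | 23.2% |
| 0.3 | 36 | 9% | 7.56 | 36.3% |
| 0.5 | 60 | 25% | 15 | 62.5% |

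**Upper bound for predicting the next order.** If every earlier order were known, the fourth in a block would always be certain and the third with probability 1/3. That is 4/3 per block, or 40 of 120. A best guess would be right 70.8% of the time. With earlier orders recognised only at rate r, the certain share of next orders is r²/3, for example 0.25/3 = 8.3% at r = 0.5.

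**Other block sizes, with all earlier orders known.** The certain share is 33% for fixed blocks of 4, 25% for 6 and 20% for 8. For a random mix of 4, 6 and 8, the simulated best-guess rate is 67.9% against 70.8% for fixed 4.

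**Timing.** Nothing can be recognised until lenses are worn, some weeks after colorimetry. Trial status estimates 1 February to 1 July 2026, which is 150 days. With 30 blocks, a block fills in 150/30 = 5 days if enrolment uses the whole span. It fills in about 60/30 = 2 days if three months are kept for follow-up. If enrolment took a full year, it would fill in 365/30, about 12 days.

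**Cost of giving up exact balance.** The worst case with blocks of 4, 6 and 8 is a final block of 8 cut after four identical orders: 58 + 4 against 58, so 62/58. The variance ratio is (1/62 + 1/58)/(2/60) = 1.001, a rise of about 0.1%. A paired comparison that ignores period would carry (62 − 58)/120 = 1/30 of any period difference. The planned mixed model includes period and so removes it.

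**The case against.** A reader might infer that any single recognised tint reveals the other orders in its block. It does not: one recognition shifts the odds to 2:1 and fixes nobody.

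A reader might also infer that predictable orders bias who is entered under which order. The timing makes this unlikely. On the stated dates a block would usually be full before any of its members wears a lens. The first-tint comparison that could be affected is described as low-powered and confirmatory. The main contrast cannot be affected this way, since every participant receives both tints. Nor does the article state outright that the lead researcher enrols. It places that person at eligibility testing and in contact at consent, and no more.

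The other objections are fair and limit the size of the point:
- The effect depends wholly on r. At r = 0.1 the block adds about one participant in 120. At r = 0.5 direct recognition already unmasks half, and block size is the lesser problem.
- Primary outcomes are diaries and questionnaires graded by participants. Secondary outcomes come from masked parents and teachers. Only the WRRT is scored by the observer, and it is tertiary and exploratory.
- Safeguards exist: others hold and apply the list, a technician rather than the research optometrist checks the tints, and the control colour is similar to the optimal one.
- Varying the block size lowers the best-guess rate only slightly.

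What stands is that the stated safeguards neither address recognition by the researcher who ran the colorimetry nor prevent deduction from a published block size. The stated benefit, exact balance, is worth little here. The plan recruits 120 to secure 88, so balance among those analysed is not guaranteed in any case.

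**Conclusion.** The point holds as a conditional weakness in assessor masking. The fixed, disclosed block of 4 contradicts nothing in the article, and its balance claim is arithmetically right. But if the tester recognises some tints, it carries part of that knowledge to participants whose tint was not recognised. The added certain orders number about 1, 4, 8 and 15 of 120 at r = 0.1, 0.2, 0.3 and 0.5, and none at r = 0. These figures assume one unstratified list, a tester who knows the block size, and recognitions that are independent and correct. The exposure is to WRRT scoring, contact at visits and the preferred-pair decision. The documents do not support reading it as a material threat to the primary within-participant comparison. It is an optional improvement, worth making because it is cheap now.

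**What to change.** Before the first participant is entered:
- Regenerate the list with randomly varying block sizes, for example 4, 6 and 8. Keep both the list and the sizes with the list holders only.
- Under Sequence generation, replace the block size of 4 with: *randomly varying block sizes not disclosed to the researcher who tests participants*. Do not print the sizes.
- Remove the statement that a multiple of 4 guarantees equal numbers in the first period.

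The cost is one new list, a short protocol amendment by the stated ethics route, and a registry update. Trial status says recruitment has not begun, so no participant is affected. The statistical price is the possible split of at worst about 62/58, with negligible loss of precision. The mixed model with period and sequence, already planned, should be used for the tint comparison so that a small imbalance does not let a period difference through.

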### Implementation

Participants will be given participant numbers in sequence. The lead researcher (ZR) will undertake colorimetry and will send the results for each participant to AW. For each participant, AW will provide NT with the PTL specification for the optimal and sub-optimal tints. BE will provide a list of randomisation codes to NT, specifying for each participant number whether the first pair should be the optimal or sub-optimal colour. NT will organise the ordering of the PTL with the dispensing team at Cerium. ZR will conduct all participants’ testing and will be unaware of whether the optimal tint is worn first or second.

### Who will be blinded

The lead researcher, trial participants, parents/guardians, teachers, and all members of the research team involved in the statistical analysis will be masked. During the statistical analyses, tints will be referred to as A and B and the code, identifying A or B as the optimal/sub-optimal, will only be broken once the statistical analysis is completed.

### Plans for assessment and collection of outcomes

Please see Additional file 3.

### Data management

Please see Additional file 3.

### Confidentiality

Data from the optometric testing and visual stress testing will be kept safe within the university eye clinic as per GDPR, and the records will not be removed from the university clinic setting. The research data, which includes colorimetry data of participants of the crossover trial, will be fully anonymised, and data files for analysis by members of the research team will, in addition to anonymisation, be password protected.

### Plans for collection, laboratory evaluation, and storage of biological specimens for genetic or molecular analysis in this trial/future use

Not applicable, there will be no use of biological specimens in this study.

Initially, all data will be checked by scatter plots of raw data. All data will be tested for normality using the Shapiro-Wilk test, and non-parametric data will be transformed to parametric where possible. Simple comparisons will use paired *t*-tests, or the Wilcoxon signed-rank test as appropriate. For more complex analyses, a Mixed-Effects Model for Repeated Measures (MMRM) will be carried out to account for the crossover design, including fixed effects (intervention type, period, and sequence) and random effects (participant variability).

A confirmatory check will be performed to test for order effects (e.g. whether participants who have the optimal tint after the sub-optimal tint have a statistically different outcome from those who have the sub-optimal tint after the optimal tint). If such an effect is found, key analyses will be repeated whilst controlling for the order effect. In addition, an analysis of the effects of the first tint alone will be compared across participants. The analysis will have low power and will be confirmatory, but it is independent of order effects.

Participants for whom there is a complete set of symptom diary data for at least 2 weeks of wear with both interventions will be analysed on an intention-to-treat basis (ITT) [44]. In the unlikely event that any participants are misallocated, then key analyses will also be run according to a per protocol approach. For the symptom questionnaire conducted before enrolment in the trial and for the academic behaviour surveys, data will only be analysed for participants for whom data are available for *both*interventions [44].

Sensitivity analysis will also be carried out to confirm the robustness of the data produced.

The secondary outcome survey measures will be converted to numeric values. Scores will be aggregated and averaged across surveys and then prepared for statistical analysis using the approaches described above. Tertiary outcome measures will be assessed separately as an exploratory analysis. Tertiary outcome measures will undergo reliability testing using the intraclass correlation coefficient, and analysis for order effects using repeated measures ANOVA, before comparing interventions using standard *t*-tests.

All statistical analyses will be conducted using R (version 4.3.1, R Core Team 2023).

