## Discussion

A protocol is outlined for a double-masked, randomised, controlled, crossover clinical trial (RCT) involving young people aged 9–18 years who meet contemporary diagnostic criteria for VS. The trial will investigate whether PTLs prescribed using the IS are beneficial. Systematic reviews [13, 20] in 2016 criticised the lack of consistent diagnostic criteria and in response criteria were published in 2017 [2]. This clinical trial will be the first study of children to adopt these diagnostic criteria. Both major reviews on this topic agree that more clinical trials are required to establish whether PTLs confer a clinical benefit in the treatment of VS.

A strength of this study is the decision to use symptoms as the primary outcome measure, which is strongly justified by the literature, and the development of a symptom questionnaire based on the literature to identify and quantify symptoms of VS. VS is a construct that is not observable or measurable directly; in statistical terms, it is a latent variable that is accessible only through certain measurable indicator variables, such as the frequency/severity of symptoms. Therefore, to support the idea that the overarching construct is valid, there was a requirement for a symptom questionnaire to be created with several VS indicators from published research [2, 10, 13]. A symptom questionnaire for VS has recently been developed for adults [45], but none is available for children and hence the development of the approach described in Methods.

A notable strength of this study is its pragmatic design, which allows data collection to occur across different phases of the school academic year, depending on the date of participant enrolment, as the study extends over 3 months. This introduces natural variation in academic and visual demands, creating differences in PTL usage and reflecting real-world use of PTLs. It captures the potential benefits of PTLs in managing VS symptoms during study-related tasks and daily visual activities. This design enhances the generalisability and real-life relevance of the results. For practical reasons, all participants will not start at the same time, but rather, enrolment in the study will be staggered over many months. Therefore, randomisation of tint allocation to wear period will average out any effects of holidays.

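### The headline tint comparison is chosen by a normality test and an order test, and no analysis is named as primary although a suitable crossover model is already in the plan

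*Protocol article*

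**What the plan says.** All of this is in the protocol article, under Statistical methods for primary and secondary outcomes, unless another section is named.

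- Normality step: "All data will be tested for normality using the Shapiro-Wilk test, and non-parametric data will be transformed to parametric where possible".
- Simple comparisons use a paired t-test or a Wilcoxon signed-rank test, whichever is judged appropriate.
- Crossover model: "For more complex analyses, a Mixed-Effects Model for Repeated Measures (MMRM) will be carried out to account for the crossover design". Its fixed effects are intervention, period and sequence, and participant is random.
- An order-effect check follows. Key analyses are repeated with control for order only if that check finds an effect. A first-period comparison is added as a low-power confirmation.
- The primary question is symptoms with pair A against pair B, measured by diary and by questionnaire, with one aggregate score for each. Neither is tied to a named test or model.
- The Sample size section uses an AB/BA crossover formula with the "within-subjects standard deviation of symptom scores", "a 0.05 probability of a type I error" and "a statistical power of 0.90". It arrives at 88, raised to 120 for withdrawals.
- The Discussion says of running across the school year: "This introduces natural variation in academic and visual demands, creating differences in PTL usage and reflecting real-world use of PTLs".

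**The concern.** Two data-driven steps stand between the data and the headline result. The first is a normality test that decides whether to transform and whether to use a t-test or a rank test. The second is an order test that decides whether order is controlled at all.

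These options do not answer the same question. A t-test on the raw score estimates a mean difference in symptom points. A t-test on a transformed score estimates a difference on another scale. The signed-rank test concerns the centre of symmetry of the differences. The reader cannot tell in advance which of these will be the result for either primary outcome.

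An unadjusted paired test also has no place for period. In an AB/BA design, a shift between months moves the A-minus-B difference one way in one sequence and the other way in the other. The paired t-test reads that spread as noise. If the sequences end up unequal in size, part of it also enters the estimate.

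**Working it through.** **Inputs.** From Sample size: two-sided 0.05, power 0.90, effect 0.5 SD, the SD being within-subject (σ_w). From Design and methods: 1:1 allocation. Assumed, because the documents give no value: a period effect π (period 2 minus period 1) of 0, 0.5 or 1.0 σ_w, and a completer split of 48:40.

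**1. The plan's own figure.** The printed formula gives n = 2(1.2816 + 1.9600)²/0.5² = 84.06, so 85. The t-based calculation for the period-adjusted contrast has standard error σ_w√(2/N) and N − 2 degrees of freedom. Its power is 0.8999 at N = 86, 0.9032 at N = 87 and 0.9065 at N = 88. It first reaches 90% at 87, and 88 is the next even number and a multiple of the block size of 4. The stated 88 is thus consistent with a period-adjusted analysis.

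**2. Unadjusted paired t-test, 44:44, σ_w = 1.** The A-minus-B difference has mean 0.5 − π in one sequence and 0.5 + π in the other, with variance 2 within each.

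- True variance of the mean difference: 2/88 = 0.0227, whatever π is, because the shifts cancel.
- Average variance that the paired t-test estimates: (2 + π² × 88/87)/88.

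At π = 0.5 the estimated standard error is √(2.2529/88) = 0.160, against a true 0.151. At π = 1.0 it is √(3.0115/88) = 0.185. With critical value 1.988, the difference needed for significance is 0.318 and 0.368. Approximate power is Φ((0.5 − 0.318)/0.1508) = 0.886 and Φ((0.5 − 0.368)/0.1508) = 0.81. Simulation agrees:

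| Period effect (σ_w) | Paired-t power | Paired-t type I error | Period-adjusted power |
|---|---|---|---|
| 0 | about 91% | about 5% | 90.7% |
| 0.5 | about 88.5% | about 3.8% | 90.7% |
| 1.0 | about 81% | about 1.6% | 90.7% |

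With all 120 participants and balance, simulated paired-t power is 97.1%, 96.2% and 92.5%, against 97.0% adjusted.

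**3. Unequal sequences.** The bias of the unadjusted mean difference is π × (48 − 40)/88 = 0.09π in size. That is 0.045 σ_w at π = 0.5 and 0.09 σ_w at π = 1.0. The main analysis set needs diary data with both tints, and going from 120 to 88 allows (120 − 88)/120 = 26.7% loss, so some imbalance is plausible. The split itself is an assumption.

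**4. The normality gate, N = 88, 4,000 simulated null trials for each case.** With normal differences, Shapiro-Wilk rejects in 4.5% of runs, and the two-stage procedure has type I error 5.3%. With heavy-tailed symmetric differences (t with 4 df), it switches to Wilcoxon in 67% of runs, and type I error is 4.9%. With skewed differences of mean zero, it switches in almost every run. Wilcoxon then rejects in 23% to 34% of runs, against about 6% for the t-test, because it tests a different quantity. This last case shows that the estimand moves with the gate. It is not a forecast of the trial's error rate.

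**The case against.** The strongest reply is that the right model is already in the article. A comparison of A with B in a crossover can be read as exactly what the mixed-model sentence covers, and naming one primary analysis is often left to a statistical analysis plan, which is not shown. This stands in part: a reader might infer that the paired t-test is the primary analysis, but the article never says so. What remains is that the article itself states a data-dependent choice of test and a conditional order adjustment. A later plan that followed it would inherit both.

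A reader might also infer that type I error is inflated. The documents do not support that. The article offers a t-test or a rank test; it does not say to run every candidate and quote whichever is significant. The two-stage rule holds close to 5% when differences are symmetric, as expected under a strict null. Analysts also see only codes A and B until the analysis is complete, so the choice of test cannot be steered towards the optimal tint.

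Nor does ignoring period make the estimate itself more variable when sequences are balanced. Only its reported standard error grows, so treating the period effect as extra sampling variance would overstate the power loss. The article also does not say that normality is tested on raw scores rather than on differences: only the scatter plots are described as of raw data.

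Finally, the Discussion notes that enrolment is staggered and that randomisation will average out holiday effects. To the extent that starts are staggered, calendar variation is within-person noise that a period term cannot remove. A period effect is therefore possible, for example from repeated diary keeping, but its size is unknown.

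**Conclusion.** The concern holds in a limited form. The article fixes a procedure in which the data choose the test, the scale and whether order is controlled, and it names no primary analysis for either primary outcome. That is a stated rule, not merely missing detail.

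The cost in power depends on a period effect that the documents do not quantify. With 88 balanced completers it is nil at zero, about 2 points at 0.5 σ_w and about 10 points at 1.0 σ_w, and the test becomes conservative. The estimate is unbiased when sequences are balanced. Under an assumed 48:40 split, it is biased by 0.09 of the period effect. No inflation of type I error is shown. The change should be made because the headline result ought to be fixed in advance and the better method is already written in the same section.

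**What to change.** - Name the mixed model already described (tint, period and sequence fixed, participant random), on the untransformed aggregate score, as the single primary analysis of the diary outcome and of the questionnaire outcome.
- Make period adjustment unconditional, so that it no longer depends on the order check.
- Remove the Shapiro-Wilk step as the way to choose the primary test, and check model residuals instead.
- Label any transformed or rank-based analysis as a sensitivity analysis.

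The cost is wording and one degree of freedom for period. The Trial status section says that recruitment has not begun, so the change can be made before any data exist.
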